**Figure 1 F1:**
[figure not shown]
Study design and patient recruitment (N = projected numbers). MBI-SS, Maslach Burnout Inventory-Student Survey; PIEF, Personal Information and Eligibility Form (PIEF); PGWB-S, Psychological General Well-Being index-short version; BPNSFS, Basic Psychological Need Satisfaction and Frustration Scale; ERI-SQ, Effort-Reward Imbalance student questionnaire; CERQ-18, Cognitive Emotion Regulation Questionnaire-Short Version; DIRE, Difficulties in Interpersonal Emotion Regulation (DIRE); Brief-Cope, Coping Orientation to Problems Experienced; MSPSS, The Multidimensional Scale of Perceived Social Support.

### Screening and recruitment

Potential participants will be invited electronically via email to students' listservs, on a weekly basis until target enrolment will be reached. In this e-mail, potential participants will receive written information on the screening aims and those who provide written consent with screening participation will fill out the PIEF and the MBI-SS. Eligible participants identified in the screening phase will be contacted by a researcher and invited to a brief assessment interview to further evaluate their eligibility based on a psychologist's rating, to give oral and written information about the clinical trial and obtain informed consent to the clinical training. Then, participants will be randomized to PC or WL groups by a colleague not involved in the study, using a computerized randomization generator. The research team will be blind to the randomized allocation.

### Outcomes data collection

Outcome variables will be assessed at T1, T2, and T3, using a Google Form. At each time, participants of the two groups will be required to fill in the eight self-report questionnaires described above (MBI-SS, PGWB-S, BPNSFS, ERI-SQ, CERQ-18, DIRE, Brief-Cope, and MSPSS). Baseline data (T1) will be collected after brief assessment interview (once informed written consent has been obtained by the participant). T2 data will be collected after the end of the last PC session. Finally, 3 months after the end of PC, participants will be contacted electronically via email and invited to fill in the Google Form to obtain T3 data.

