### Aims, hypotheses, and study design

The present study is a randomized clinical trial aimed at generating evidence in support of the effectiveness of an online group psychological counseling intervention in university students with high levels of academic burnout. To this aim, the study design entails the comparison between students that will be randomly assigned to two matched groups: (1) a psychological counseling group (PC, *N* = 65) or (2) a waiting list control group (WL, *N* = 65). We will test the effect of time (pre-PC vs. post-PC) in interaction with the effect of group (PC vs. WL) on the score obtained in several self-report outcome measures, including scores on burnout symptoms, general wellbeing, and academic achievement as primary outcomes. We hypothesize that PC, compared to WL, should provide evidence of the efficacy of psychological counseling to decrease burnout symptoms and improve general wellbeing and academic achievement.

Moreover, to acquire data on possible mediators or psychological change, we will also assess a large set of secondary outcome variables potentially related to academic burnout, including effort-reward imbalances, basic psychological needs of satisfaction/frustration, intrapersonal and interpersonal emotion regulation, coping strategies and social support. Such variables will be directly and/or indirectly addressed in the psychological counseling sessions (see Section “Intervention” and Table 1). We hypothesize that secondary outcomes variables may be affected by the psychological counseling intervention, mediating or moderating its effects on primary outcomes.

**Table 1 T1:** Summary of psychological counseling intervention features.

**Session**	**Strategy**	**In-session activities**	**Treatment goals**	**TA techniques**
First	Psychoeducation	Information provision on stress, burnout, and coping Information provision about intervention action and goals	Self-awareness	Contract
	Agreement treatment goals	Set goals for time in treatment	Self-awareness	
	Promotion of social support	Introduction of participants and personal experiences sharing	Social support	Therapeutic alliance/group cohesion
Second	Psychoeducation	Information provision on psychological basic needs Identification of basic needs and their satisfaction or frustration in the academic context	Self-awareness	Strokes Therapeutic alliance/group cohesion

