### Intervention

The online group psychological counseling will be provided to small groups of maximum 10 participants. The intervention will consist of 6 weekly group sessions of 2 h each, based on Transactional Analysis model (Stewart and Joines, 1987; Cannavale and Castagna, 2018). Each session will be conducted by certified psychotherapists trained in Transactional Analysis and an observer co-conductor. In line with treatment goals, intervention strategies will include: (a) psychoeducation about academic-related stress, burnout, and effective strategies to contrast burnout; (b) interventions to promote self-awareness of personal reactions to academic-related stressful events, of the connection between different levels of such reactions (thoughts, emotion, bodily sensations, and behaviors), of psychological satisfaction/frustration needs, and of maladaptive habitual behaviors (e.g., learning style) which may influence academic burnout; (c) intervention to promote initial cognitive restructuring aimed at the identification of more helpful cognitive representations of academic context events (especially cognitive representations of self and others); (d) promotion of social support encouraging social sharing and adaptive social interaction in the group. See Table 1 for an overview of strategies, in-session activities, consistency with treatment goals, and the related TA concepts/techniques.

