### Statistical analysis

Descriptive statistics will be reported for participant recruitment, acceptance, adherence, and dropout rates. Baseline characteristics for each group will be reported to ensure group matching on these variables. To verify the reliability of the eight questionnaires, we will compute test-retest correlations between T1 and T2, and between T1 and T3 (using Pearson's *r* coefficients).

To assess the effects of PC on the outcome variables (MBI-SS, PGWB-S, and academic achievement), mixed model regressions will be utilized, by considering Time (T1, T2, and T3) and Group (PC vs. WL) as fixed factors and subjects as the random factor. This technique will allow us to test the interaction between Time and Group. Our expectation is that PC and WL should differ at T2 and T3, but not at T1, indicating that the PC group should achieve higher scores than the WL group after, but not before, the psychological counseling intervention.

A series of path analyses will be conducted to determine whether the measures obtained from the BPNSFS, ERI-SQ, CERQ-18, DIRE, Brief-Cope, and MSPSS questionnaires mediate the differences in the outcome variables between T1 and T2, and T1 and T3. For each analysis, the exogenous variables will be the outcome measures at T1, the mediators will be the scores in the subscales of the BPNSFS, ERI-SQ, CERQ-18, DIRE, Brief-Cope, and MSPSS questionnaires, and the endogenous variables will be the outcome measures at T1. Since each questionnaire involves multiple subscales, two separate models will be computed for each mediator. For example, for the BPNSFS questionnaire, we will test whether the Autonomy Satisfaction, Competence Satisfaction, Relatedness Satisfaction, Autonomy Frustration, Competence Frustration, and Relatedness Frustration subscales will mediate the associations between the T1 and T2 (or T1 and T3) outcome measures.

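### The T1–T2 path models have no mediator score taken after counseling starts and before the T2 outcome, so they can show concurrent association but not mediation

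*Protocol article*

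**What the plan says.** All from the protocol article:

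- **Waves** (Outcomes data collection): "Outcome variables will be assessed at T1, T2, and T3, using a Google Form". On content: "At each time, participants of the two groups will be required to fill in the eight self-report questionnaires described above". Two of the eight questionnaires are outcomes (MBI-SS, PGWB-S); the other six are the proposed mediators.
- **Timing** (same section): for T1, "Baseline data (T1) will be collected after brief assessment interview"; for T2, "T2 data will be collected after the end of the last PC session"; for T3, "Finally, 3 months after the end of PC, participants will be contacted electronically via email".
- **Treatment period** (Intervention): "The intervention will consist of 6 weekly group sessions of 2 h each". No assessment is described during these weeks.
- **Hypothesis** (Aims, hypotheses, and study design): the secondary variables may be affected by counseling, "mediating or moderating its effects on primary outcomes".
- **Analysis** (Statistical analysis): path models will test whether the mediator scales "mediate the differences in the outcome variables between T1 and T2, and T1 and T3". The wave of the mediator score is not stated.

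**The concern.** A mediator has to be changed by treatment and then change the outcome, so its measurement should follow the start of treatment and precede the outcome. Students who feel less burned out at T2 may, for that reason alone, also report better need satisfaction, coping and support. If both are measured together, this reverse route looks the same as mediation.

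At stake is the reading of the mediation hypothesis. A T1–T2 indirect effect could be presented as what counseling works through when it is only a by-product of the improvement.

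**Working it through.** **1. Schedule against models.**

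| Model | Mediator score | Position | Can it be a mediator of the treatment effect? |
|---|---|---|---|
| T1–T2 | T1 | before treatment | No: treatment cannot have changed it |
| T1–T2 | T2 | same form as the outcome | Direction cannot be established |
| T1–T3 | T2 | after treatment, before the T3 outcome | Yes, as far as time order goes |

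Waves after treatment start and before the outcome: 0 for T2, 1 for T3. The extra MBI-SS at screening (T0) precedes treatment and changes nothing. The PGWB asks about the last 4 weeks, so its T2 score can reach back into the six-week course, before the T2 mediator score was given.

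**2. The plan's own figure.** The illustrations borrow d = 0.50 from Participants and sample size. The exact two-sided t-test at 0.05 gives power 0.801 with 64 per arm, so the stated 128 is reproduced. It is not in dispute.

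**3. Illustration: apparent mediation when the truth is none.** Assumptions not in the documents: counseling (G) acts on burnout only, Y2 = 0.5G + e; the mediator only follows burnout, M2 = r·Y2 + u; within-arm variances are 1; arm is in the model.

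- Path from arm to mediator: a = 0.5r. Path from mediator to outcome given arm: b = r.
- Apparent proportion mediated: ab/0.5 = r². For r = 0.3, 0.5, 0.7 this is 9%, 25%, 49%. Simulation (n = 400,000) gave 0.090, 0.252, 0.498.

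**4. At trial size, with T1 adjustment.** Assumptions: 65 per arm, arm effect 0.5 SD, adjustment for T1 mediator and T1 outcome, both paths required to be significant, 4,000 runs.

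| Assumed path | 0.3 | 0.5 | 0.7 |
|---|---|---|---|
| Mediator is only a consequence: indirect effect declared | 19% | 37% | 54% |
| Same case: mean indirect effect (truth 0) | 0.055 | 0.124 | 0.198 |
| Mediator is the mechanism: indirect effect declared | 88% | 90% | 91% |

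A positive T1–T2 result is therefore compatible with either direction.

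**5. How clean is the T2-mediator, T3-outcome model?** Take the step 3 scenario. Let s be the T2-to-T3 outcome slope and p the reliability of the measured T2 outcome.

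- Without adjustment for the T2 outcome, and ignoring T1 terms, the mediator coefficient is s·r. With s = 0.6 (assumed): 0.18, 0.30, 0.42.
- With adjustment for the T2 outcome it is s·r·(1 − p)/(1 − p·r²). If p = 1 this is 0. The article gives MBI-SS subscale reliabilities of 0.86, 0.82 and 0.77. With p = 0.82 and s = 0.6:
  - r = 0.3: 0.0324/0.9262 = 0.035
  - r = 0.5: 0.0540/0.7950 = 0.068
  - r = 0.7: 0.0756/0.5982 = 0.126

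Adjusting for the T2 outcome removes most of the spurious coefficient, but not all of it.

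**The case against.** **The wave of the mediator is a detail for the full protocol or SAP.** This stands for T1–T3: the article's silence there is not an error, and the scheduled data support the right choice. It does not rescue T1–T2, because an analysis plan can choose among waves but cannot create one.

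**The article makes no strong mechanism claim.** It speaks of possible mediators, and its limitations paragraph concedes only partial understanding of mechanisms. This lowers the stakes. However, that paragraph blames the lack of an active control, which is a different problem, and the planned T1–T2 models are still described as mediation.

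**The r² figures describe a model the article does not write.** Correct. Its path models start from the T1 outcome and do not include group. They also name the T1 outcome at both ends. Those are separate defects; repairing them leaves the timing gap in place. The percentages are illustrations under assumed correlations, and a reader who took them as the bias to expect in this trial would go beyond the documents.

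**Reverse causation is less plausible for academic achievement.** Partly fair: the mood-based route is less direct for exams passed and grades. But exams passed before the T2 form also precede the T2 mediator score, so time order is not secured there either.

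**Adjusting T3 for the T2 outcome answers a different question.** This stands. A mechanism that did its work during the six sessions is already in the T2 outcome and is adjusted away. That version therefore belongs as a sensitivity analysis, with its limit stated.

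**Conclusion.** The point holds for the T1–T2 path models. They have no mediator score that follows treatment start and precedes the outcome, so they cannot tell mechanism from consequence even if otherwise correctly specified. This follows from the schedule alone; the size of any false indirect effect rests on assumed correlations and paths.

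Four stronger readings are tempting but not supported:

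- That all the planned mediation fails. For T1–T3 the T2 score has the right time order.
- That a T2-to-T3 analysis gives a clean zero when there is no mediation. That needs an error-free T2 outcome; under the assumptions in the working it is about 0.04 to 0.13.
- That the efficacy result is compromised. The primary Time by Group test uses no mediator.
- That a mid-course assessment is required. It would add a procedure for a secondary analysis, and the reporting can be put right without it.

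The form is shared within each wave; that mediators and outcomes are answered on the same day is an inference from this.

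**What to change.** 1. Report the T1–T2 path results as concurrent association and do not call them mediation.
2. In the T1–T3 models, use the T2 mediator score, with group as the exposure and adjustment for the T1 mediator and T1 outcome.
3. As a sensitivity analysis, report a version that also adjusts for the T2 outcome. State that it tests only mechanisms of change after treatment ends, so a null result does not exclude a mechanism acting during the six sessions, and that measurement error in the T2 outcome leaves a small coefficient in the spurious direction.
4. Confirm that waiting-list students remain untreated until T3, which the text shown does not say; the between-arm T3 models depend on it.

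The cost is a change to the analysis text, using data already scheduled. The T1–T2 mediation claim is given up. Neither T1–T3 version is decisive alone: the first still carries the reverse route through the T2 outcome, and the second can remove a true early mechanism.

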### Intervention

The online group psychological counseling will be provided to small groups of maximum 10 participants. The intervention will consist of 6 weekly group sessions of 2 h each, based on Transactional Analysis model (Stewart and Joines, 1987; Cannavale and Castagna, 2018). Each session will be conducted by certified psychotherapists trained in Transactional Analysis and an observer co-conductor. In line with treatment goals, intervention strategies will include: (a) psychoeducation about academic-related stress, burnout, and effective strategies to contrast burnout; (b) interventions to promote self-awareness of personal reactions to academic-related stressful events, of the connection between different levels of such reactions (thoughts, emotion, bodily sensations, and behaviors), of psychological satisfaction/frustration needs, and of maladaptive habitual behaviors (e.g., learning style) which may influence academic burnout; (c) intervention to promote initial cognitive restructuring aimed at the identification of more helpful cognitive representations of academic context events (especially cognitive representations of self and others); (d) promotion of social support encouraging social sharing and adaptive social interaction in the group. See Table 1 for an overview of strategies, in-session activities, consistency with treatment goals, and the related TA concepts/techniques.

### Statistical analysis

Descriptive statistics will be reported for participant recruitment, acceptance, adherence, and dropout rates. Baseline characteristics for each group will be reported to ensure group matching on these variables. To verify the reliability of the eight questionnaires, we will compute test-retest correlations between T1 and T2, and between T1 and T3 (using Pearson's *r* coefficients).

To assess the effects of PC on the outcome variables (MBI-SS, PGWB-S, and academic achievement), mixed model regressions will be utilized, by considering Time (T1, T2, and T3) and Group (PC vs. WL) as fixed factors and subjects as the random factor. This technique will allow us to test the interaction between Time and Group. Our expectation is that PC and WL should differ at T2 and T3, but not at T1, indicating that the PC group should achieve higher scores than the WL group after, but not before, the psychological counseling intervention.

A series of path analyses will be conducted to determine whether the measures obtained from the BPNSFS, ERI-SQ, CERQ-18, DIRE, Brief-Cope, and MSPSS questionnaires mediate the differences in the outcome variables between T1 and T2, and T1 and T3. For each analysis, the exogenous variables will be the outcome measures at T1, the mediators will be the scores in the subscales of the BPNSFS, ERI-SQ, CERQ-18, DIRE, Brief-Cope, and MSPSS questionnaires, and the endogenous variables will be the outcome measures at T1. Since each questionnaire involves multiple subscales, two separate models will be computed for each mediator. For example, for the BPNSFS questionnaire, we will test whether the Autonomy Satisfaction, Competence Satisfaction, Relatedness Satisfaction, Autonomy Frustration, Competence Frustration, and Relatedness Frustration subscales will mediate the associations between the T1 and T2 (or T1 and T3) outcome measures.

We will also calculate Reliable Change Index (RCI) and Clinically Significant Change (CSC) (Jacobson and Truax, 1991) for each patient, from pre- to post- treatment and at follow-up. The RCI is computed as a ratio in which the numerator represents the difference between each subject's pretest and post-test outcome scores, while the denominator represents the standard error of the difference between the two test scores. According to Jacobson and Truax (1991), RC indices larger than 1.96 indicate that a significant change has occurred. The CSC is represented by a patient's score moving from the “dysfunctional population” range into the “functional population.” For example, pre-treatment to post-treatment of at least 2 standard deviations from the original mean (Evans et al., 1998). Finally, we will provide grouped percentages (PC vs. WL) for those individuals who reliably improved or had a clinically significant change.

The study is based on substantial evidence that psychological interventions promoting self-awareness, cognitive restructuring, and social support are effective strategies to combat burnout. This provides a strong foundation for the research. The study applies these interventions to the specific case of academic burnout, a field that is promising but still lacks strong evidence from randomized controlled trials. In the present article, we described the research protocol of the first randomized controlled trial to determine the efficacy of an online group psychological intervention specifically designed for university students with high levels of burnout. Moreover, we gave attention to several methodological issues. In line with the empirically supported psychological treatments requirements (Chambless and Hollon, 1998), we propose a between-group design with adequate statistical power, and we clearly specified sample characteristics (defined by standard measures). We also identified a large range of possible primary and secondary outcomes, and we planned the implementation of statistical analyses suitable for the understanding of different levels of effects in the data that will be collected.

Beside such strengths, the research protocol has also few weaknesses. First, we planned a waiting list design without active control conditions, such as psychological placebo and/or another treatment control groups. We opted for a waiting list design because it is widely used in standard pragmatic trials (Purgato et al., 2015) and it presents relevant ethical advantages (it allows for the provision of care to all research participants). However, due to the lack of an active control condition, our understanding of the mechanisms underlying any possible effect of the intervention will be necessarily partial (Barkauskas et al., 2005; Hart et al., 2008). This could potentially limit the internal validity of the study. Second, according to empirically supported treatments movement (Chambless and Hollon, 1998), experiments must be conducted with treatment manuals. Even if we refer to existing Transactional Analysis manuals to design the psychological intervention, due to the novelty of the field of application a dedicated manual for academic burnout is still missing (but currently in progress). This could lead to inconsistencies in the delivery of the intervention, making it harder to replicate the study and understand which specific aspects of the intervention are most effective. Third, due to the sample size and the group format only an exiguous number of psychotherapists will conduct the interventions. We will control for the effect of the provider in statistical analysis, but our sample size will not allow a complete evaluation of “therapist effects” (Crits-Christoph and Mintz, 1991). The fact that only a small number of psychotherapists will conduct the interventions could introduce therapist effects, where the outcomes are influenced by the specific therapists' skills, styles, or personalities. While the study plans to control for the effect of the provider in statistical analysis, the small sample size may not allow for a complete evaluation of these effects. Finally, while the sample size of 130 participants may be sufficient for detecting large effects, it may not be large enough to detect smaller, yet still meaningful, effects. This could limit the statistical power of the study and the ability to generalize the findings to a larger population. Future studies should overcome such limitations.

In conclusion, while the study does have a few weaknesses, such as the lack of an active control condition, the absence of a dedicated manual for academic burnout, and the limited number of psychotherapists conducting the interventions, these limitations are acknowledged and provide avenues for future research to build upon this work. Overall, the strengths of this study make it a potentially significant contribution to the field. This would draw more attention to academic organizational politics and related supporting actions.

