### Participants and sample size

Assuming a medium effect size (Cohen's *d* = 0.50), we estimated with the G^*^Power3 software (Faul et al., 2007) that we need a sample size of 128 participants (i.e., two groups of 64 students) to achieve a power of 0.80 (α = 0.05). Thus, a total of 130 students will be recruited from bachelor's courses at Universitas Mercatorum. Participants are eligible for inclusion according with the following criteria: (a) age > 18 years; (b) clinical levels of academic burnout scores [one standard deviation above the mean MBI-SS total score reported in the validation study by Portoghese et al. (2018)]; (c) attendance of 1^st^ or 2^nd^ year of bachelor course at Universitas Mercatorum; and (d) sufficient knowledge of the Italian language. Additional exclusion criteria aimed at selecting a sufficiently homogeneous group of participants are: (a) previous university degree; (b) other psychiatric diagnoses; (c) other ongoing psychological or psychiatric treatments. Finally, we also excluded (d) attendance of 3^rd^ year of bachelor course, to avoid participants drop-outs due to the course conclusion.

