## Instruments

### Screening instruments

#### Maslach burnout inventory-student survey

The MBI-SS (Schaufeli et al., 1996; Italian adaptation: Portoghese et al., 2018) is a 15-item self-report questionnaire composed of three subscales: Exhaustion (EX; item example “*I feel used up at the end of a day at university*”), Cynicism (CY; item example “*I doubt the significance of my studies*”), and Professional Efficacy (PE; item example “*During class I feel confident that I am effective in getting things done*”). All the items are scored by using a 7-point Likert scale ranging from 0 (=“*never*”) to 6 (=“*always*”). We will use the Italian version of MBI-SS from the study of Portoghese et al. (2018), in which reliability coefficients for each of the subscale scores were 0.86 for EX, 0.82 for CY and 0.77 for PE. The MBI-SS will be used to select students with high levels of academic burnout.

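### The questionnaire reliability check uses T1–T2 and T1–T3 correlations that span the counseling and are not limited to the waiting-list arm

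*Protocol article*

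**What the plan says.** The Statistical analysis section of the Protocol article states the purpose and the method together: to check that the eight questionnaires are reliable, "we will compute test-retest correlations between T1 and T2, and between T1 and T3". Pearson coefficients are to be used. No arm is named, so as written the check covers all participants.

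The timing comes from two other sections. Outcomes data collection places T1 before the counseling and says that "T2 data will be collected after the end of the last PC session"; T3 follows three months later. The Intervention section gives the length: "The intervention will consist of 6 weekly group sessions of 2 h each".

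The same article expects scores to move over these intervals. Statistical analysis expects the arms to differ at T2 and T3 but not at T1. Aims, hypotheses, and study design says the secondary variables may also be affected by the counseling.

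Two further statements bear on the point. The section on the Maslach burnout inventory (MBI-SS) cites an external source of reliability: "reliability coefficients for each of the subscale scores were 0.86 for EX, 0.82 for CY and 0.77 for PE". Participants and sample size defines entry as "one standard deviation above the mean MBI-SS total score", taken from the same validation study.

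**The concern.** A test-retest correlation estimates reliability only if true scores keep their relative positions between the two occasions. Here one arm is treated in between, and the trial is built on the expectation that treatment changes scores. Any difference in true change between students, whether between arms or within the counseling arm, lowers the correlation exactly as measurement error would, and the coefficient cannot tell the two apart.

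The better and the more unevenly the counseling works, the less reliable the questionnaires will appear. All eight are exposed, because each measures either an outcome or a proposed mediator. At stake is the reliability statement in the trial report. The Reliable Change Index (RCI) would also be affected if the same correlation were carried into its standard error.

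**Working it through.** The plan states no reliability for this trial and no numerical RCI threshold, so there is no figure of its own to reproduce. The size of the effect has to be illustrated under assumptions.

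**Inputs**
- Treatment-free correlation r0 = 0.82. This borrows the Cynicism coefficient from the MBI-SS section. Treating it as the T1–T2 correlation without treatment is an assumption.
- Arm difference at T2, d = 0.5 in T1 SD units. This is the effect size in Participants and sample size.
- SD of individual response in the counseling arm, s. The documents do not give it; it is varied from 0 to 0.7.
- Also assumed: equal arms, T1 SD and untreated T2 SD both 1, and response independent of the T1 score.

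**Step 1, counseling arm.** The T1–T2 covariance stays at r0, while the T2 variance becomes 1 + s². So r = r0 / √(1 + s²). With s = 0.5: 0.82 / √1.25 = 0.733.

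**Step 2, arms pooled.** Half the sample carries the response variance, and the arm difference adds d²/4. So r = r0 / √(1 + s²/2 + d²/4). With s = 0.5: 0.82 / √(1 + 0.125 + 0.0625) = 0.82 / 1.090 = 0.752.

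| Response SD s | Counseling arm | Pooled |
|---|---|---|
| 0 | 0.820 | 0.796 |
| 0.3 | 0.785 | 0.779 |
| 0.5 | 0.733 | 0.752 |
| 0.7 | 0.672 | 0.717 |

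A uniform shift leaves the correlation within the counseling arm untouched, but pooling still lowers it slightly. Most of the loss comes from variation in response.

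**Step 3, effect of selection.** In a simulation with normal scores, entry above +1 SD, reliability 0.82 and no true change, the later measurements have SD 0.68 and correlate 0.61. Selection alone thus lowers the coefficient. It leaves the standard error of a difference intact if both quantities come from the selected sample: 0.68 × √(2 × (1 − 0.61)) = 0.60, against the true √(2 × 0.18) = 0.60. Pairing the validation coefficient with the selected-sample SD gives 0.68 × √(2 × 0.18) = 0.41, which is too small. The 1.96 rule would then sit at 1.96 × 0.41 / 0.60 ≈ 1.33 true standard errors, and about 18% of unchanged students, not 5%, would be flagged as changed.

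**Step 4, RCI, only if the spanning correlation were used.** In SD units the bar is 1.96 × √(2(1 − r)). This is 1.18 at r = 0.82 and 1.38 at r = 0.752, a rise of about 0.2 SD.

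**Step 5, precision of a waiting-list estimate.** With 65 students and r = 0.82, Fisher's transformation gives atanh(0.82) ± 1.96/√62 = 1.157 ± 0.249, that is, 0.72 to 0.89.

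**The case against.** The best defence is that the damage is confined. The sentence gives the correlations a purpose of their own, the primary comparison is a mixed model that does not use them, and the RCI and Clinically Significant Change (CSC) results are descriptive percentages by arm. That all stands, and it limits the weight of the point. It does not rescue the check itself, which is stated in full and does not measure what it claims to measure.

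A reader might go further and infer that the RCI thresholds are wrong because these correlations feed them. The article does not say so. It describes the RCI only by saying that "the denominator represents the standard error of the difference between the two test scores", names no reliability or SD, and does not refer back to the test-retest correlations. Published coefficients are cited elsewhere and could serve. An article may leave that choice to the full plan. If one pooled correlation were used, the bar would rise in both arms, so the error would be conservative and not confined to the counseling arm.

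A reader might also infer that the CSC rule measures distance from the selected sample's own mean and must be replaced. The wording is "pre-treatment to post-treatment of at least 2 standard deviations from the original mean". It is offered as an example, and the population behind that mean is not named. The governing definition is a move from the dysfunctional to the functional range. Two SD from the dysfunctional group's mean is a recognised form of that criterion, so preferring another cut-off is a choice between accepted options, not the correction of an error.

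Selection above +1 SD might likewise be counted against the RCI. Step 3 shows that it does no harm there when the coefficient and SD come from the same sample.

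**Conclusion.** The concern holds for the reliability check. Correlations across the counseling, taken without restriction to the waiting-list arm, do not verify reliability, and they will understate it if students respond unequally. In the illustration 0.82 becomes about 0.75 pooled, with a range of 0.80 to 0.72 as the response SD goes from 0 to 0.7. The response SD, the starting value of 0.82 and the independence of response from baseline are assumptions; if response depended on the T1 score, the figures would differ. T1–T3 adds three further months of real change.

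The documents do not support a claim that the RCI or CSC thresholds are wrong. What follows for the RCI is conditional: if a reliability is needed, the treatment-spanning correlation is the wrong one to use. The consequences reach the reliability statement and possibly the descriptive responder percentages. The mixed-model analysis is not touched.

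**What to change.** Replace the sentence on test-retest correlations so that:

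- reliability of each questionnaire is estimated by internal consistency at T1 in all participants;
- if test-retest is also reported, it uses T1–T2 in the waiting-list arm only, with a note that it rests on about 65 students and still includes natural change;
- T1–T3 correlations, if kept, are labelled as stability over time and not as reliability.

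Where a reliability enters the RCI, name the coefficient and the SD and take both from one source: T1 internal consistency with the T1 SD, or the validation coefficient with the validation SD. The article gives validation coefficients for the three MBI-SS subscales only, so a total-score RCI on that route would need the total's own coefficient.

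The cost is wording; no data collection changes. There are two drawbacks. Internal consistency says nothing about stability over weeks. The waiting-list correlation is also imprecise: its interval at 0.82 runs from 0.72 to 0.89, so it should be reported with its confidence interval. A T1 value below the published coefficients should be read with the restricted entry range in mind.
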